### Sample size

The primary efficacy analysis will assess the non-inferiority of the clinical cure rate of SCT compared with LCT. The margin of non-inferiority is set at 10% on the statistically acceptable tolerance and clinically acceptable margin. This margin has been used as accepted in the field of infectious diseases [12, 13]. Because non-inferiority clinical trials in infectious diseases usually cannot rely on previous placebo controlled trials to calculate and estimate inferiority margins, we decided to use the rather arbitrary number of 10% as is conventionally employed. Regarding clinical cure, we judged the margin to likely be acceptable to most patients. The non-inferiority of SCT is concluded if the upper limit of the one-sided 97.5% confidence interval (CI) for the difference in clinical response (standard SCT) is less than 10%. To achieve a power of 80% with an α level of 2.5%, assuming as stated in the previous retrospective study a clinical cure rate of 95% with standard therapy with the same cure rate in SCT [6], with a non-inferiority margin of − 10%, 75 patients are required in each group.

### Statistical analysis

We will analyse data using both ITT and per-protocol analyses. The per-protocol analysis population will consist of all randomized patients who are not lost to follow-up and have no major protocol deviations. We will attest the non-inferiority of the primary outcome on the basis of the normal theory test for binomial proportions. We will conduct the primary analysis without adjustment of potential confounders.

Secondary outcomes will also be analysed under a non-inferiority assumption, as appropriate. Pre-defined subgroup analyses for the primary and secondary outcomes include (1) presence or absence of septic shock at diagnosis; (2) presence or absence of bacteraemia; (3) initial antibiotics covering or not covering causative organisms; (4) Gram-positive organisms causing cholangitis; and (5) quick Sequential Organ Failure Assessment (qSOFA) score.

Clinical outcomes are confirmed by the investigators either by calling the patients by telephone or seeing them at an outpatient clinic visit, or by checking the clinical chart if the patient is still hospitalized.

All *P* values are one-sided, and *P* < 0.025 is considered statistically significant. All statistical analyses will be performed using STATA version 15.0 (StataCorp, College Station, TX, USA), and R version 3.5.1 (the R Foundation for Statistical Computing, Vienna, Austria).

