**Methods/design:**

We will conduct a multi-centre, open-label, randomized, non-inferiority trial to compare short-course therapy (SCT) with conventional long-course therapy (LCT) in treating patients with acute cholangitis. SCT consists of 5-day intravenous antimicrobial therapy if the patients had clinical improvement, while at least 7 days of intravenous antibiotics will be provided to the LCT group. The primary outcome is clinical cure at 30 days after onset. Patients will be randomly assigned in an open-label fashion. A total sample size of 150 was estimated to provide a power of 80% with a one-sided α level of 2.5% and a non-inferiority margin of 10%.

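### At the protocol's own design point (95% cure in both arms, 10-point margin, 75 per arm), a one-sided 2.5% level and 80% power cannot both be met

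*Protocol article*

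**What the plan says.** The design figures are in the protocol article, under Sample size and in the Methods/design part of the Abstract. The planning assumption is "a clinical cure rate of 95% with standard therapy with the same cure rate in SCT". The margin is 10 percentage points, the level is one-sided 2.5%, the target power is 80%, and the result is 75 per group. The Abstract repeats this: "A total sample size of 150 was estimated to provide a power of 80" per cent. Non-inferiority is declared when the upper one-sided 97.5% confidence limit for the difference in cure (read here as LCT minus SCT) is below 10%.

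The Statistical analysis section names the test: "We will attest the non-inferiority of the primary outcome on the basis of the normal theory test for binomial proportions". The primary analysis is unadjusted, and both ITT and per-protocol sets are analysed. The article does not say whether the variance is unpooled or restricted to the null hypothesis.

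**The concern.** At 95% cure, 75 patients give 75 × 0.05 = 3.75 expected failures per arm. On the null boundary (LCT 95%, SCT 85%) they give 3.75 and 11.25. With proportions this close to 1, the observed failure counts drive the estimated variance, and the normal-theory variants behave quite differently. A level and a power taken from the large-sample formula may then not be those of the test actually applied.

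Two things are at stake. One variant declares the shorter course non-inferior more often than the stated 2.5% when it is truly 10 points worse. The other holds the error but gives the trial clearly less than the stated chance of success. Because the wording fits either, one dataset near the boundary could support opposite conclusions.

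**Working it through.** **Inputs (Sample size; Statistical analysis).** One-sided α = 0.025 (z = 1.96), power 0.80 (z = 0.8416), cure 0.95 in both arms, margin 0.10, n = 75 per arm, 1:1 allocation.

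**1. Reproduce the plan's figure.** Unpooled normal formula:
n = (1.96 + 0.8416)² × (2 × 0.95 × 0.05) / 0.10² = 7.849 × 0.095 / 0.01 = 74.56, so 75 per arm. Approximate power at 75 is 80.2%. The plan's arithmetic is correct for this formula.

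Other normal-theory formulas do not give 75:
- With continuity correction: 93.5, so 94.
- Score (Farrington-Manning): the null-restricted rates are 0.9703 and 0.8703, so n = (1.96 × √(0.9703 × 0.0297 + 0.8703 × 0.1297) + 0.8416 × √0.095)² / 0.01 = (0.738 + 0.259)² / 0.01 ≈ 99.4, so 100.

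**2. Exact operating characteristics at 75 per arm.** All 76 × 76 outcomes were enumerated under two binomials. Error is the probability of declaring non-inferiority when SCT is exactly 10 points below LCT. Power is the same probability at 95%/95%.

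| Method | Error, LCT 90% | 95% | 97% | 99% | Power at 95%/95% |
|---|---|---|---|---|---|
| Wald (unpooled) | 3.0% | 3.7% | 4.5% | 5.6% | 81.7% |
| Score (null-restricted) | 2.3% | 2.0% | 2.0% | 2.1% | 68.6% |
| Newcombe | 2.5% | 2.6% | 2.4% | 2.2% | 71.8% |

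Over the whole null boundary the score test's largest exact error is about 2.65% (Farrington-Manning form). At every LCT rate checked from 85% upwards it is 2.4% or less.

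**3. Could some other test reach both figures?** Take the single null point LCT 97.2% / SCT 87.2%. By the Neyman-Pearson lemma, the best possible 2.5% test of that point has 72.3% power against 95%/95%. Any test that holds 2.5% over the whole null must hold it there, so its power at 75 per arm cannot exceed 72.3%. The 80% target is out of reach at this level and sample size.

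**4. Does the choice affect a verdict?** Take LCT 73/75 and SCT 71/75, a difference of 2/75 = 0.0267.
- Wald: standard error √[(0.9733 × 0.0267 + 0.9467 × 0.0533)/75] = 0.0319. Upper limit 0.0267 + 1.96 × 0.0319 = 0.089, below 0.10: non-inferior.
- Score: restricted rates 0.983 and 0.883, standard error √[(0.983 × 0.017 + 0.883 × 0.117)/75] = 0.040. z = (0.0267 − 0.10)/0.040 = −1.84, which does not reach −1.96: not shown.
- Newcombe: upper limit 0.105, above 0.10: not shown.

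Score and Newcombe both pass at 72/75. Under 95%/95%, Wald passes and score fails in 13.1% of trials. Wald passes and Newcombe fails in 9.9%.

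**The case against.** The strongest reply is that the protocol never names Wald. A planning formula does not bind the analysis, and the variance form is commonly left to the statistical analysis plan, which is not shown. That stands. A reader might infer that the trial will claim non-inferiority at an inflated error rate, but the document does not support this: the inflation is conditional on Wald being used. The reply does not remove the inconsistency. Level, power, sample size and test family are all fixed in the protocol, and either usual variance choice misses one of the stated figures.

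Other limits also stand.
- A reader might take 3.7% as a floor for Wald. It applies at LCT cure of 95% or more. Below that the excess is smaller: 3.3% at 93% and 3.0% at 90%.
- The power shortfall belongs to the 95% assumption. If true cure in both arms were 97%, the score test would have 84.0% power with error still about 2.0%.
- Wald and score are not the only options. Agresti-Caffo, for example, gives 2.7% and 75.5%. None reaches 80% while holding 2.5%.
- The methods disagree only on borderline results, by one SCT patient in the example above.
- A reader might add that per-protocol exclusions lower power further. That is a separate matter. The article gives no exclusion rate, so any such figure would rest on an assumed one.

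**Conclusion.** The point holds at the protocol's own design assumptions and is an inconsistency in what is written, beyond mere missing detail. With 95% cure in both arms, a 10-point margin and 75 per arm, the plan can have about 80% power with a true error near 3.7% (Wald), or an error near 2.0% with about 69% power (score). Newcombe gives 2.6% and 72%. The stated pair of 2.5% and 80% is not available.

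The sample-size arithmetic itself is not wrong; 75 is right for its formula. The fault lies in treating the large-sample level and power as those of the actual test with so few failures. The figures assume independent binomial outcomes and all 75 patients per arm analysed.

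**What to change.** In the Statistical analysis section, name the Farrington-Manning/Miettinen-Nurminen score limit, one-sided 97.5%, as the primary method for both the ITT and per-protocol analyses. Note that its exact error is about 2.0% at the design point and at most about 2.65% over the null.

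In the Sample size section and the Abstract, replace the 80% with the power of that method at 75 per arm: about 69% at 95% cure, with 84% at 97% cure as a sensitivity figure. The Newcombe interval is an acceptable alternative, with about 72% power at 95% cure, if its level is described as approximately 2.5%. Any per-protocol power figure should be left out or labelled as resting on an assumed exclusion rate.

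The change is to wording and should be made before the outcome data are analysed; the named software, Stata and R, can do the calculation. The downside is a less favourable stated power. No extra patients are needed.

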### Randomization and allocation concealment

Patients are randomly allocated to each treatment arm at a 1:1 ratio before or within 24 h after initiating antimicrobial therapy. Randomization will be performed using a stochastic minimization procedure centrally at the study centre (Division of Infectious Diseases Therapeutics, Kobe University Graduate School of Medicine). We will use an electronic data capture system to conduct randomization and data collection.

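### Allocation is by minimisation but the primary analysis is fixed as unadjusted; if the minimisation factors predict cure, a little precision is given away

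*Protocol article*

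**What the plan says.** Under Randomization and allocation concealment, the article states: "Randomization will be performed using a stochastic minimization procedure centrally at the study centre". The ratio is 1:1. The article does not name the minimisation factors.

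Under Statistical analysis, non-inferiority of clinical cure is to be tested "on the basis of the normal theory test for binomial proportions", and the next sentence settles the role of covariates: "We will conduct the primary analysis without adjustment of potential confounders".

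Under Sample size, the calculation assumes "a clinical cure rate of 95% with standard therapy with the same cure rate in SCT", with a 10-point margin, one-sided α of 2.5% and 80% power. It arrives at 75 per group.

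**The concern.** Minimisation makes the arms alike on the chosen factors. When a factor predicts outcome, that balance removes part of the chance variation in the difference between arms. The ordinary two-proportion standard error treats the arms as independent simple samples and does not register this, so it is larger than the true sampling variability. An analysis stratified by the same factors would recover the difference.

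The article goes further than leaving the model to a later document: it rules adjustment out of the primary analysis. At stake is some avoidable loss of precision in a trial whose calculated power has almost nothing above 80%. There is also a mismatch between how patients are allocated and how they are compared.

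**Working it through.** **Inputs.** From Sample size: cure 95% in both arms, margin 0.10, one-sided α 0.025, power 80%, 75 per arm. The factors and their prognostic strength are not given, so everything that depends on them is an assumption shown as a range.

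**1. The plan's own figure.** With unpooled binomial variance and no covariates:

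n = 2 × 0.95 × 0.05 × (1.960 + 0.842)² / 0.10² = 74.6, rounded up to 75 per arm.

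SE = √(2 × 0.95 × 0.05 / 75) = 0.0356; half-width = 1.96 × 0.0356 = 6.98 points; power = Φ(0.10/0.0356 − 1.96) = 80.2%.

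The figure reproduces exactly on the unadjusted variance.

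**2. What a balancing factor can remove.** For a two-level factor with shares w and 1 − w and cure rates that differ by d, the share of outcome variance explained is R² = w(1 − w)d² / (0.95 × 0.05). The adjusted SE is 0.0356 × √(1 − R²).

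| Assumed cure by level (split) | R² | Half-width, points | Power by formula | n per arm |
|---|---|---|---|---|
| no effect | 0 | 6.98 | 80.2% | 75 |
| 97% vs 93% (50:50) | 0.8% | 6.95 | 80.6% | 74 |
| 99% vs 91% (50:50) | 3.4% | 6.86 | 81.6% | 73 |
| 100% vs 90% (50:50) | 5.3% | 6.79 | 82.3% | 71 |
| 98% vs 83% (80:20) | 7.6% | 6.71 | 83.2% | 69 |
| 99% vs 79% (80:20) | 13.5% | 6.49 | 85.6% | 65 |

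At 95% cure, an evenly split factor cannot exceed R² = 5.3%. Larger values need a minority subgroup with much lower cure.

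**3. Simulation under minimisation.** Settings: 150 patients, biased coin 0.8, two binary factors of which one is prognostic, overall cure 95%, no true difference, 8,000 runs per row. SEs are root mean squares.

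| Assumed cure by level | Unadjusted SE | True SD of unadjusted difference | Mantel-Haenszel SE | Power, unadjusted → stratified |
|---|---|---|---|---|
| no effect | 0.0353 | 0.0356 | 0.0353 | 80.7% → 80.9% |
| 99% vs 91%, 50:50 | 0.0354 | 0.0350 | 0.0348 | 80.8% → 81.6% |
| 98% vs 83%, 80:20 | 0.0353 | 0.0344 | 0.0339 | 82.0% → 83.6% |
| 99% vs 79%, 80:20 | 0.0355 | 0.0333 | 0.0329 | 82.4% → 85.5% |

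The unadjusted SE stays near 0.035 while the true SD falls, and the stratified SE follows it. The gain from stratifying is 0.2, 0.8, 1.6 and 3.1 points of power. In the strongest setting this is less than step 2 suggests, because the balanced unadjusted estimate is itself less variable and already has some extra power.

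**4. How far stratification can be pushed.** Expected failures are 150 × 0.05 = 7.5, or about 4 per arm. When many factors were crossed into 20 cells and the factors were weak, simulated power fell to about 77%, below the unadjusted analysis.

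**The case against.** The strongest reply is that sample size and analysis agree with each other. The trial was sized on the unadjusted variance, and the unadjusted interval, about 7 points each side, is the one it was powered for. That stands. A reader might infer that the interval is wider than the design allows, or that the trial is underpowered without adjustment. The documents support neither: nothing in them relies on a narrower interval, and 80.2% is delivered without one.

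Second, the loss is conditional. With no factors named, nobody can say from this article that precision is lost. The list may stand in the full protocol or analysis plan, so its absence is no criticism. A separate simulation (6,000 runs, linear regression with robust SE) found no over-wide interval for factors explaining up to (0.3 × 0.7 × 0.10² + 0.25 × 0.024²)/0.0475 = 4.7% of variance. The SD of the unadjusted difference was 0.0357 and 0.0354, against mean SEs of 0.0348 and 0.0349. The mean SE sits a little below the root mean square used in step 3, which partly hides the effect. Even so, the result confirms that for moderate factors the effect is close to invisible.

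Third, a reader might infer a threat to the trial's error rate. An over-wide interval cannot cause a false claim of non-inferiority. In that same simulation, at a true 10-point deficit, the unadjusted test rejected in 3.5% to 3.7% of runs and the adjusted one in 3.5% to 3.8%. That excess over 2.5% comes from the Wald interval at high cure rates. It is a separate matter, which adjustment neither causes nor cures.

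What remains is that the article positively excludes factors which the trial already balances on, and that including them sensibly costs little.

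**Conclusion.** The point holds as a minor one. Allocation by minimisation is paired with a primary analysis fixed as unadjusted. If the factors predict cure, the unadjusted standard error is somewhat too large and roughly 0 to 3 points of power are forgone. The upper end needs a strong factor, such as 99% vs 79% cure in an 80:20 split. A factor giving 97% vs 93% in equal groups changes the formula power only from 80.2% to 80.6%. These sizes rest on assumed prognostic strengths, two-level factors and a biased coin of 0.8. The direction is conservative, and the stated sample size and power are met without adjustment.

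**What to change.** Replace the sentence on adjustment under Statistical analysis. The primary risk difference should be stratified by the minimisation factors with Mantel-Haenszel weights and a score-type interval, and the unadjusted difference kept as a sensitivity analysis. State a small number of strata and a rule for pooling sparse ones before any outcome data are seen. Include a rule for small centres only if centre is in fact a minimisation factor, which the article does not say.

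The cost is one or two sentences and a few lines of code, since the factors are already held for randomisation. The downside is the one shown in step 4: with about 8 expected failures, crossing too many factors loses precision, so the strata have to be few. Settling this beforehand also matters because the trial is open-label with investigator-judged cure, and an adjustment chosen after the results are known would be open to challenge.

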### Exclusion criteria

The exclusion criteria are that:
The patient did not provide written informed consent.Any biliary duct obstruction was not removed.Treating physicians or the investigators judged that inclusion in the study was inappropriate.

The presence of bacteraemia is not an exclusion criterion.

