### Trial interventions

The antibiotics given to the study participants should be commercially available and approved for use in Japan. They will be used at the marketed accepted dosage as indicated in each package insert. The initial antibiotics will be selected at the discretion of either the treating physician or the consultant infectious disease doctor. Selected antibiotics can be changed to other antibiotics during the treatment based on culture/susceptibility tests results or potential adverse reactions that are suspected or occurred in the patient. Dose adjustments based on patients’ renal function or other criteria are performed as judged appropriate and necessary by the consultant infectious disease doctors.

In the SCT group, intravenous antibiotics will be continued at least for 5 days, and can be discontinued if all of the following criteria are fulfilled: (1) maintenance of body temperature under 37.8 °C for more than 48 h, (2) systolic blood pressure above 90 mmHg, (3) heart rate below 100 beats/min, (4) respiratory rate below 24 breaths/min, and oxygen saturation at room air above 90%. In the LCT group, intravenous antibiotics will be given for the duration of usual care, at least for 7 days, at the discretion of both the treating gastroenterologists and the consultant infectious disease doctors, provided that there are no biliary duct obstructions remaining, as stated in the inclusion/exclusion criteria. In the SCT group, positive blood culture results will not alter the duration of the treatment unless other complications which necessitate prolongation of the treatment, such as abscess or infective endocarditis, occur and either the treating physicians or the consultant infectious disease doctors remove the patient from the intervention. These patients will still be included in the analysis on an intention-to-treat (ITT) basis but will be excluded from the per-protocol analysis. The schedule of assessments is shown in Fig. 2.

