## Discussion

The current trial will examine whether SCT for acute cholangitis with appropriate biliary duct drainage is not inferior to conventional LCT. A retrospective cohort study with propensity score analysis suggested that the efficacy of SCT as well as occurrence of complications are similar to those of LCT [6]. If non-inferiority was achieved, SCT has several advantages over LCT in terms of length of hospital stay, potential adverse effects from antimicrobial therapy, cost, and emergence of antimicrobial resistance [7–10].

The current proposed trial has some inherent limitations. First, for practical reasons, we were not able to design the study to be double-blinded. Both patients and investigators will know to which group the patients belong. However, we consider that the outcomes we set are obvious and would not be likely to be impaired significantly by the trial being an open-label design, as demonstrated in a previous similar study [14]. Second, since clinical outcomes will be judged by our investigators, there is an inherent issue of potential subjectivity on outcome judgement. On the other hand, based on the previous study with a very high cure rate, we believe this is a relatively small problem unlike treatments of diseases with a lower success rate. In addition, it is not practical to employ independent investigators in multi-centre settings. Third, because this study is conducted solely in Japan, although it is a multi-centre trial, the results of the study might not be applicable in different settings outside the country. The results of the proposed study are not applicable to those patients with acute cholangitis when bile duct obstruction remains.

To the best of our knowledge, this will be the first trial to answer the clinical question of whether shortening of antimicrobial therapy for the treatment of acute cholangitis is possible without impairing treatment safety and efficacy. We hope that the trial aids in establishing a novel therapy to optimize the duration of antibiotic therapy for this rather common disease.

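### The coverage subgroup (initial antibiotics covering or not covering the causative organism) can be decided after open allocation, so for patients randomised before their first dose it is not a baseline subgroup

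*Protocol article*

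**What the plan says.** The Statistical analysis section lists five subgroups for the primary and secondary outcomes. The first carries a time point: "1) presence or absence of septic shock at diagnosis". The next three are "2) presence or absence of bacteraemia; (3) initial antibiotics covering or not covering causative organisms; (4) Gram-positive organisms causing cholangitis", and the last is "5) quick Sequential Organ Failure Assessment (qSOFA) score".

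Three other statements bear on subgroup (3):

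- Randomization and allocation concealment: "Patients are randomly allocated to each treatment arm at a 1:1 ratio before or within 24 h after initiating antimicrobial therapy".
- Trial interventions: "The initial antibiotics will be selected at the discretion of either the treating physician or the consultant infectious disease doctor".
- Discussion, on the open-label design: "Both patients and investigators will know to which group the patients belong".

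**The concern.** A subgroup comparison keeps the protection of randomisation only if allocation cannot affect who belongs to the subgroup. Coverage joins two things: the organism, which is a property of the patient's illness, and the drug, which is a decision. If the decision is taken when the arm is known, doctors may choose differently in the two arms. A doctor who expects a short course might, for instance, choose a broader agent. The covered patients in short-course therapy (SCT) would then not be the same kind of patients as the covered patients in long-course therapy (LCT). A difference between arms within the subgroup could reflect who was placed there and not the length of treatment.

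At stake is one of the five pre-defined subgroup results. Readers would look to it to learn whether a short course is adequate when the first drug was or was not active.

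**Working it through.** **1. Order of events.** I take the initial antibiotic to be the first one given. The randomisation window then yields two kinds of patient.

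| Randomised | When the first antibiotic is chosen | Can the arm influence the choice? |
|---|---|---|
| After the first dose, within 24 h | Before allocation | No |
| Before the first dose | Possibly after allocation | Yes: the choice is discretionary and the arm is known |

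The article does not say how many patients fall in each row. Nor does it say that the choice must be made or recorded before the arm is released.

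**2. What determines the distortion.** Suppose treatment length has no effect on cure. Among patients with an isolate, let:

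- f = share randomised before the first dose;
- d = share of those whose status changes from not covered to covered because they are known to be in SCT;
- C = share covered without any such influence, with cure rate p;
- u = cure rate of the remaining share, 1 − C;
- r = cure rate of the patients who move when they are covered, and r′ = their cure rate when they are not.

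In the covered stratum, cure is p in LCT and (C·p + f·d·r)/(C + f·d) in SCT. The spurious difference, SCT minus LCT, is

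f·d·(r − p)/(C + f·d).

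In the not-covered stratum it is

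f·d·(u − r′)/(1 − C − f·d).

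Both vanish if f = 0 (nobody randomised before the first dose) or d = 0 (knowing the arm never changes coverage). The first also vanishes if r = p and the second if u = r′, that is, if the patients who move are typical of the stratum. The article gives none of these quantities, so I put no numbers in. The formulas show the conditions for a distortion and do not estimate one.

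**3. What is not touched.** The primary comparison uses all randomised patients by arm (or the per-protocol set) and does not use coverage. The sample size reproduces from the article's inputs (95% cure in both arms, margin 10 points, one-sided 2.5%, power 80%):

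n = (1.960 + 0.842)² × 2 × 0.95 × 0.05 / 0.10² = 7.85 × 0.095 / 0.01 = 74.6, rounded up to 75 per group.

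Power at 75 per group is 80.2%. Nothing in this point changes that figure.

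**The case against.** **The case for leaving subgroup (3) alone.** The arms differ in duration and not in drug, and one selection rule applies to both. The article gives no reason to expect that knowing the duration would shift the choice, and patients who have already had a dose are safe. All of this is fair, and it keeps the point small. It does not remove it: the choice is discretionary and the arm is known, so comparability rests on doctors' behaviour where it could rest on the design. A later analysis plan could relabel the analysis. It could not restore the order of choice and allocation for patients already randomised.

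**A stronger reading the documents do not support.** A reader might infer that bacteraemia and Gram-positive organisms are also post-randomisation subgroups, because no culture window is stated. A positive culture at relapse would then move a failed patient into the bacteraemia stratum and could shift a harm from one stratum to the other. No passage says that bacteraemia at relapse counts, and the context points the other way:

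- The Exclusion criteria treat it as a feature at entry: "The presence of bacteraemia is not an exclusion criterion".
- Trial interventions discusses positive blood cultures in relation to the index treatment.
- Subgroup (4) concerns the organisms responsible for the cholangitis, and recurrence is listed separately as an outcome.

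An organism in a specimen taken at diagnosis is a pre-treatment attribute even if the laboratory reports it after randomisation. A numerical example built on counting later cultures would therefore show nothing about this plan.

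**Missing time points in general.** Nor does the absence of a time point make a subgroup faulty. The qSOFA score has none in that section either, and the natural reading is again baseline. A culture window or assessment time is detail that a condensed article may leave to the full protocol or analysis plan, and the schedule of assessments (Fig. 2) is not shown.

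**Conclusion.** The point holds for subgroup (3) only. For patients randomised before their first dose, the article allows the antibiotic that defines the subgroup to be chosen with the arm known, so that comparison is not protected by randomisation. This follows from reading the randomisation, intervention and blinding statements together and needs no assumption about cultures. Whether a material bias arises depends on the share of such patients and on whether doctors act on the allocation, and the article informs neither. I rate it minor: it affects how far one subgroup result can be trusted, and not the trial's main conclusion.

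**What to change.** Define subgroup (3) by the antibiotic given or ordered before allocation, and have the electronic data capture system require that entry before it releases the arm. Judge coverage against the organism from the diagnostic culture. This records the doctors' choice and does not restrict it.

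The first patient was recruited on 27 June 2019, so some patients may already have been randomised before their first dose without such a record. For them, report (3) as a post-randomisation, exploratory analysis, and state how many they are.

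The cost is one short field before allocation, one sentence in the analysis section, and incomplete data on this variable for patients already enrolled. No extra patients are needed.

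The same sentence could state that subgroups (2), (4) and (5) use specimens or assessments from diagnosis. That is a harmless clarification and does not correct an error.
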